#### Additional Measures

To evaluate possible confounding variables, the following constructs are measured: *Childhood Trauma*, measured by the Childhood Trauma Questionnaire (CTQ; Bernstein & Fink, 1998), which will be administered during the baseline measurement as ImRs interventions were originally developed for intrusive memories following traumatic events; *Time of intervention*: Time interval (in days) between the participants’ regular CBT session and the study therapy session for each of the three intervention sessions; *Comorbid disorders*, as measured with the SCID-5-CV interview at the outpatient clinic before the start of the study;

*Therapeutic techniques* used in patients’ routine therapy, as well as the *amount of regular therapy sessions* received during the study period, will be recorded via a questionnaire sent to the treating therapists at the outpatient clinic after the patient has completed the final follow-up assessment (FU2). The CBT conducted alongside the study intervention is part of routine clinical care and not part of the study protocol. It follows a naturalistic format without a standardized manual, predefined number of sessions, or fixed structure. Consequently, the dose and content of CBT may vary between participants. To monitor potential overlap with imagery-based methods, the therapist questionnaire includes items assessing whether, and to what extent, imagery techniques or imagery rescripting were used during the course of therapy.

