### Data Analyses

To address the longitudinal nature of our data and potential missing values, we will employ a multilevel approach. This method allows us to model individual trajectories of change over time while accounting for between-person differences. The multilevel model will include time as a within-subject factor and condition as a between-subject factor. The interaction effect between time and condition is of main interest, as it will indicate whether the rate of change in depressive symptoms differs between the intervention and control group. All primary analyses will be conducted using an intention-to-treat (ITT) approach, including all randomized participants. Missing data will be handled using mixed-effects models, which are robust to missingness under the assumption of missing at random. Analysis will be conducted in R (R Core Team, 2025). In case of substantial differences between conditions in demographic or any of the potentially confounding variables listed previously (e.g., number of CBT sessions before intervention), the variable(s) will be added as covariates to the model. For the analysis of secondary outcomes (e.g., repetitive negative thinking, emotional capabilities, self-compassion, self-esteem), we will employ a similar multilevel modelling approach. Each secondary outcome will be analysed separately, with time and condition as predictors, and the time-by-condition interaction as the primary effect of interest. Given the number of secondary outcomes, we will apply a correction for multiple testing to mitigate the risk of Type I errors across models. Effect sizes will be reported alongside *p*-values to aid interpretation. Results will be treated as exploratory, and full model outputs (including corrected and uncorrected *p*-values) will be provided in the supplementary material to ensure transparency. This will allow us to examine how these outcomes change over the course of the study and whether these changes differ between the ImRs and control conditions.

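### The covariate rule for the primary model is not limited to baseline variables: three of the five listed confounders arise after randomisation, and the form in which a covariate enters is not fixed

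*Protocol article*

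**What the plan says.** The protocol article, Data Analyses, specifies a multilevel model with time and condition, and states: "The interaction effect between time and condition is of main interest". Covariates depend on the observed data: "In case of substantial differences between conditions in demographic or any of the potentially confounding variables listed previously", in which case "the variable(s) will be added as covariates to the model". The text gives no cut-off for a substantial difference, no restriction to baseline variables, and no statement on whether a covariate is also interacted with time. The one example is the count of CBT sessions held before the intervention. The same section promises an intention-to-treat analysis of everyone randomised.

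The list referred to is in Additional Measures, which opens: "To evaluate possible confounding variables, the following constructs are measured". It has five items:

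- childhood trauma (CTQ), at baseline;
- the interval in days between the "regular CBT session and the study therapy session for each of the three intervention sessions";
- comorbid disorders, from the clinic interview before the study;
- techniques used in routine therapy;
- the number of regular sessions "received during the study period, will be recorded via a questionnaire sent to the treating therapists".

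The questionnaire that supplies the last two items is "sent to the treating therapists at the outpatient clinic after the patient has completed the final follow-up assessment (FU2"). Under Randomization, allocation follows the introduction session and so precedes all three intervention sessions.

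**The concern.** Randomisation makes a between-arm difference in a baseline variable a matter of chance. A difference in a variable that arises later is either chance or a consequence of the allocated condition. Adjusting for a consequence changes the question from the total effect of being offered ImRs to an effect with routine CBT held fixed. The rule applies exactly when such a difference is seen.

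The route is plausible here. Patients know their condition, because a video explains it to them after randomisation. Participants says that routine CBT is left free in content, structure and dose. Additional Measures expects that imagery rescripting may be used within it.

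Three further problems follow. The primary model is chosen after looking at the arms, by an undefined criterion. Two of the variables may be unavailable for participants who leave before FU2. And if covariates enter as main effects only, readers would believe that an imbalance had been corrected when the coefficient of interest had hardly moved.

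**Working it through.** The plan gives no figure for this rule. Its stated power of 85–90% involves no covariate and does not bear on the point.

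**1. Timing of the five items.** CTQ and comorbid disorders precede randomisation. The session interval is defined by the three intervention sessions, so it comes after. Regular sessions are counted over the study period, so they come after too. Techniques are reported after FU2 for a course of therapy that includes the trial period. That makes three of five open to influence by allocation. The example given in Data Analyses, sessions before the intervention, is pre-randomisation but is not on this list.

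**2. Time-constant covariate as a main effect.** Take the random-intercept structure described under Sample Size, with four occasions. For participant i at occasion t, y = (time and condition terms) + b_i + βx_i + error. In the change from baseline to FU2 the covariate contributes βx_i − βx_i = 0. With complete data the time × condition estimate is therefore the same with or without x, whatever β is and whenever x was measured.

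A simulation checked this, with N = 66 allocated 1:1 and four occasions. Assumed inputs: between-person SD 7, residual SD 5 BDI-II points, and a true direct effect at FU2 of −4.0. The covariate's effect on change is −1.0 point per occasion per SD, so −3.0 at FU2.

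| Estimate at FU2, complete data | No covariate | Main effect | Covariate × time | Time-varying |
|---|---|---|---|---|
| Baseline covariate, expected imbalance 0.5 SD (60 trials) | −5.69 | −5.69 | −4.26 | not needed here |
| Post-randomisation covariate, shifted 0.8 SD by condition (50 trials) | −6.79 | −6.79 | −4.50 | −4.97 |

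The largest difference between the first two columns was 0.0000.

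With missing visits the identity is only approximate. With 20% of follow-up values missing at random, the main effect moved the estimate by 0.02 on average (at most 0.07). With missingness driven by a baseline covariate, it moved it by 0.04 on average (at most 0.22).

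**3. Covariate × time.** For the baseline covariate, the expected error from imbalance is 0.5 × (−3.0) = −1.5. Interacting the covariate with time removed 5.69 − 4.26 = 1.43 of it, which is a proper correction of chance imbalance. For the post-randomisation covariate, the part of the effect passing through it is 0.8 × (−3.0) = −2.4, so the total effect is −4.0 − 2.4 = −6.4. Adjustment shifted the estimate by 6.79 − 4.50 = 2.29, from the total effect towards the direct one. If the condition shifted the covariate by −0.8 instead, the total effect would be −4.0 + 2.4 = −1.6, and the same adjustment would enlarge the estimate towards −4.0. The direction is not fixed.

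Monte Carlo standard errors of these means are about 0.2 to 0.3 (for example 1.87/√50 = 0.26), so the within-trial shifts are more reliable than the levels.

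**4. Covariates collected after FU2.** A mixed model fitted in R uses a participant's available outcomes, but by default it drops rows in which a covariate is missing. If the questionnaire is sent only once FU2 is complete, a participant without FU2 has no value for techniques or session count, and all of that participant's rows are lost. The article gives no drop-out rate. If 20% did not complete FU2 (assumed), 0.20 × 66 ≈ 13 participants would leave the model, whether the covariate enters as a main effect or otherwise.

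**The case against.** The strongest reply is that the article fixes little here. It says that variables are added as covariates without naming a main effect or an interaction, and a condensed article may leave that to the analysis plan. The only example is a pre-randomisation variable. Under the simple main-effect reading, the primary estimate hardly moves. All of this is fair, and it limits the point. It does not remove it, because the rule as written explicitly takes in the whole list, and three items on that list arise after randomisation.

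Stronger readings are tempting but are not supported:

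- **That the rule must be either inert or biasing.** A baseline covariate interacted with time is neither, and the rule permits it. A post-randomisation covariate distorts the estimate only with a time interaction or in time-varying form; as a main effect it is as inert as a baseline one.
- **That a main effect can never change the estimate.** This is exact only for complete data and time-constant covariates. The plan expects missing values, and the session interval is recorded for each of three sessions, so it need not be constant.
- **That any such adjustment contradicts the intention-to-treat analysis.** An inert covariate excludes nobody, and adjusting for a mediator changes the estimand, not the analysis set. The conflict arises only through missing covariate values, and that rests on the questionnaire being sent only to therapists of patients who completed FU2.
- **That a known share of the effect would be removed.** The documents give no mediated share and no direction, and an observed difference may be pure chance.

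The 0.5 SD baseline imbalance is also large. With 33 per arm the standard error of a standardised difference is √(2/33) = 0.246, so 0.5 SD is about 2.0 standard errors. At one standard error the assumed coefficient gives 0.246 × 3.0 = 0.74 points, and the unadjusted estimate remains unbiased on average over randomisations.

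**Conclusion.** The point holds as a defect in how the rule is drawn. It allows the primary model to be adjusted, on an undefined observed difference, for variables that allocation may have changed. Whether that alters the result depends on a model form the article does not state. With a time interaction or a time-varying term, the estimate can move away from the total effect in either direction by an unknown amount. As a main effect it moves by nothing with complete data and very little otherwise, so it would not correct an imbalance in change.

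The possible loss of participants without FU2 applies in any form for techniques and session counts. It is an inference from when the questionnaire is sent. The invariance with complete data is algebra and rests on no assumed size. The simulated shifts rest on assumed variances and covariate effects and illustrate direction, not expected magnitude. The rule should be redrawn before analysis; nothing here shows that the planned primary result will be wrong.

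**What to change.** Replace the imbalance trigger with a short list of pre-randomisation covariates, named in advance and included whatever the observed imbalance. The number of CBT sessions completed at study entry is the natural candidate. Its value should be fixed at entry and not taken from the questionnaire sent after FU2. State that each covariate enters with its interaction with time, or use a model adjusted for baseline BDI-II.

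Keep the session interval, routine-therapy techniques and concurrent CBT sessions out of the primary model. Report them by arm, or use them in an analysis labelled exploratory that also states how many participants lack the covariate.

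The cost is analysis-plan wording and some degrees of freedom. With four time points, a continuous covariate with its time interaction takes 1 + 3 = 4 parameters. Study therapist is optional: with four levels it would take 3 × 4 = 12, or 16 together with CBT sessions at entry, which is not negligible for 66 participants.

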### Exploratory Analyses

We will present the drop-out rate alongside descriptive statistics and include qualitative feedback from participants regarding their experiences with the study. To investigate potential mechanisms of the effects of ImRs, we will conduct mediation analyses within the multilevel framework. Specifically, we will explore whether changes in secondary outcomes mediate the relationship between the intervention condition and changes in depressive symptoms.

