In addition to the open research questions regarding the extent to which ImRs affects depressive symptoms, there is also a lack of evidence regarding the potential mechanisms that play a role in ImRs. Studies have shown some evidence for different potential mechanisms on a cognitive level that might be responsible for the effect of ImRs: One aspect that several studies point out is the positive impact of ImRs on different aspects of a person’s self-representation (Lee & Kwon, 2013; Wild et al., 2008), self-belief (Cooper, 2011) and self-esteem (Çili et al., 2017). There are study results that indicate that the negative core beliefs associated with the distressing memories reduce in subjects treated with ImRs (Reimer & Moscovitch, 2015). Mancini and Mancini (2018) suggest that the effect of ImRs is based on a reduction of the ‘meta-emotional problem’, which is linked to a better acceptance of the negative emotions associated with the distressing memories. In the treatment of posttraumatic stress disorder (PTSD) related to traumas experienced in childhood, changes in strengths of encapsulated beliefs and distress of the index trauma preceded changes of PTSD-severity in ImRs (Rameckers et al., 2024), supporting the theory that change in emotional meaning of the memory underlies the effects of ImRs. Assmann et al. (2024) investigated the role of cognitions in the treatment of childhood-related PTSD using ImRs. Their study found that changes in trauma-related cognitions significantly mediated the relationship between ImRs and reductions in PTSD symptoms. These results highlight the critical role of cognitive processes in the effectiveness of ImRs and suggest that targeting maladaptive cognitions may be a key mechanism through which ImRs facilitates therapeutic change in PTSD. Further research is needed on the effects of ImRs on different aspects of cognition and emotion as well as on the ‘meta-emotional problem’.

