Current research points to the problem that the effect of ImRs on depression has not been tested sufficiently in studies yet, especially not as an adjunct to regular cognitive behavioural therapy. Furthermore, the mechanisms of action of ImRs for depression remain unclear. This randomized controlled trial aims to expand the research on ImRs in depression. The primary objective is to evaluate the effectiveness of ImRs as an add-on to standard CBT for major depressive disorder (MDD). Patients receiving CBT in routine care are randomized to receive either three sessions of ImRs or an active control condition (imagery relaxation). We hypothesize that participants in the ImRs condition will show greater reductions in depressive symptoms from pre-intervention to post-intervention and follow-up. Although ImRs may be applicable across a range of disorders (Kip et al., 2023), we chose to focus specifically on depression in the present study for several reasons: First, the high prevalence of distressing memories among individuals with depression suggests a particularly strong clinical relevance of ImRs in this context (Brewin et al., 1996; Newby & Moulds, 2011a; Payne et al., 2019). Second, existing studies have primarily evaluated ImRs as a standalone intervention; its potential additive effect when embedded within standard CBT for depression remains largely unexplored. Third, depression continues to be among the most prevalent and burdensome mental health conditions, underlining the need for innovative adjunctive treatments. Given these considerations, we see depression as a particularly meaningful starting point for examining the clinical utility of ImRs. Importantly, comorbidities are not excluded in our study, reflecting the complex presentations often encountered in routine clinical practice. Secondary objectives of this trial include examining changes in associated psychological variables (e.g., repetitive negative thinking, emotional capabilities, self-compassion, self-esteem). In addition, exploratory analyses will investigate potential mechanisms underlying the effects of ImRs.

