#### Secondary Outcomes

We will use the following measures at every measurement (before randomization (baseline), just prior to every session, one week after the last session (post-intervention) and four weeks and eight weeks after the last session (Follow-up 1 and 2)): Depressive symptom severity, measured by the depression module of the Patient Health Questionnaire (PHQ-9; Kroenke et al., 2001); Rating (0 – 100) of the belief that the core beliefs captured in the baseline session are true; Rating (0 – 100) of the emotions that are associated with the memories and core beliefs captured in the baseline session; Rating (0 – 100) of the burden of the memories for the patient. The PHQ-9 was included alongside the BDI-II to allow for convergent validation of depressive symptom trajectories. In addition, due to its brevity and ease of administration, the PHQ-9 is used at each study session, making it possible to assess depressive symptoms at more frequent time points than with the BDI-II. This enables a more fine-grained analysis of symptom changes across the intervention period.

The following measures will be administered before randomization (baseline), one week after the last session (post-intervention) and four weeks and eight weeks after the last session (Follow-up 1 and 2): *Repetitive negative thinking*, measured by the Perseverative Thinking Questionnaire (PTQ; Ehring et al., 2011); *Emotional capabilities*, measured by the Self-Assessment of Emotional Capabilities (SEK-27; Berking & Znoj, 2008); *Self-compassion*, measured by the short version of the German Self-Compassion Scale (SVS-SV; Hupfeld & Ruffieux, 2011); *Self-efficacy*, measured by the German global self-efficacy expectancy scale (SWE; Jerusalem & Schwarzer, 1999); *Beliefs about emotions*, measured by the German version of the Emotion Beliefs Questionnaire (EBQ; Grüning et al., 2021); *Self-esteem*, measured by the German version of the Rosenberg Self-Esteem Scale (RSES; von Collani & Herzberg, 2003). At post-intervention, we will measure *satisfaction with treatment*, measured by the German patient satisfaction questionnaire (ZUF-8; Schmidt et al., 1989) adapted for the study as well as the *working alliance* between patient and study therapist, measured by the working alliance inventory (WAI; Wilmers et al., 2008). At the post-intervention assessment, the patients will also be asked in an open-response format, to what extent they think they have benefited from the study.

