## Discussion

We presented a study protocol for a randomized controlled trial testing the additional effect of ImRs on depressive symptoms in individuals who are already in treatment (CBT). We hypothesized that, compared to an active control condition, the participants receiving ImRs would have a greater reduction of depressive symptoms.

While there are pilot studies showing significant effects of ImRs on depressive symptom severity (Brewin et al., 2009; Ma & Lo, 2022), this study aims to replicate and extend these promising results. Importantly, no studies have yet examined the additional effect of ImRs during regular CBT for depression. By investigating potential synergistic effects of ImRs and CBT, this study could provide valuable insights into enhancing treatment outcomes for depression. If participants in the ImRs condition show greater improvements in depressive symptoms, it would suggest a promising avenue for augmenting existing therapies. This is particularly significant given that current treatment options for depression are often insufficient for many patients (Cuijpers et al., 2021). Another important aspect that this study attempts to clarify is the underlying mechanisms that may be involved in the effect of the ImRs technique on depressive symptoms. This study contributes to the research on potential mechanisms by assessing the change of different psychological variables during the course of the study and by analysing exploratorily whether changes in psychological variables mediate the effect of ImRs on depressive symptoms.

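### The exploratory mediation analysis fixes no time order and, as worded, admits PHQ-9 as a mediator of depression, so same-interval changes could not separate mechanism from reverse causation

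*Protocol article*

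**What the plan says.** Under Exploratory Analyses, the article states that "we will conduct mediation analyses within the multilevel framework", and specifies that "we will explore whether changes in secondary outcomes mediate the relationship between the intervention condition and changes in depressive symptoms". No lag, wave or order of mediator and outcome is given, and no secondary outcome is excluded.

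Under Secondary Outcomes, the first measure listed is "Depressive symptom severity, measured by the depression module of the Patient Health Questionnaire" (PHQ-9). Its stated purposes are convergent validation against the BDI-II and finer tracking of symptoms. Neither is a mechanism role.

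Other places describe the mediators more narrowly. The Discussion speaks of contributing to mechanism research "by analysing exploratorily whether changes in psychological variables mediate the effect of ImRs on depressive symptoms". The introduction gives self-esteem, self-compassion, emotional capabilities and repetitive negative thinking as examples of the secondary variables, and PHQ-9 is not among them.

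The introduction cites a PTSD study in which "changes in strengths of encapsulated beliefs and distress of the index trauma preceded changes of PTSD-severity in ImRs", and takes this as support for the theory of how ImRs works. The status of the mechanism work is clear: "exploratory analyses will investigate potential mechanisms underlying the effects of ImRs".

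**The concern.** Randomization protects the path from condition to mediator. It does not protect the path from mediator to depression. When change in a scale is related to change in BDI-II over the same interval, the data cannot show which moved first. A patient whose mood lifts will usually also report better self-esteem, less rumination and weaker negative beliefs. That pattern gives an indirect effect even if these variables do nothing to depression.

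PHQ-9 is the extreme case. As a mediator it would show that depression explains depression.

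At stake is a stated aim of the trial: "Another important aspect that this study attempts to clarify is the underlying mechanisms". An exploratory label lowers the certainty claimed, but it does not make a circular or order-free result informative about mechanism.

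**Working it through.** **1. Which measures fall in the set, and when they are taken** (Primary Outcome and Secondary Outcomes sections)

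| Measure | Taken at | Change score possible? |
|---|---|---|
| BDI-II (outcome) | baseline, post, FU1, FU2 | yes |
| PHQ-9 | the same four, plus before each session | yes, but same construct as the outcome |
| Core-belief, emotion and memory-burden ratings | the same four, plus before each session | yes |
| PTQ, SEK-27, self-compassion, SWE, EBQ, RSES | baseline, post, FU1, FU2 | yes |
| ZUF-8, WAI | post only | no |

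The wording therefore admits PHQ-9, while ZUF-8 and WAI drop out because they have no baseline. A time order is available from data already planned. The ratings exist before each session. All repeated scales are taken at post (week 1 after the last session), which is 4 − 1 = 3 weeks before FU1 and 8 − 1 = 7 weeks before FU2.

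**2. What same-interval analysis gives when there is no mediation**

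The article states no figure for this analysis, so there is none to reproduce. Apart from N = 66 with 33 per arm, every input below is an assumption.

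- Depression at baseline: Y0, variance 0.7² + 0.7² = 0.98 (SD about 1).
- Depression at post: Y1 = 0.6·Y0 − eff·A + error with SD 0.8, where A is the arm.
- Candidate mediator at each wave: M = c·Y + noise with variance 1 − c². M has no effect on Y.

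The within-arm variance of change in Y is V = (0.6 − 1)² × 0.98 + 0.8² = 0.1568 + 0.64 = 0.7968. The expected paths are:

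- a (arm to change in M) = −c·eff
- b (change in M to change in Y, given arm) = cV / [c²V + 2(1 − c²)]
- total effect = −eff

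The spurious proportion mediated is a·b/total = c²V / [c²V + 2(1 − c²)]:

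- c = 0.5: 0.1992 / (0.1992 + 1.50) = 0.12 (simulated median 0.10)
- c = 0.6: 0.2868 / (0.2868 + 1.28) = 0.18 (simulated 0.17)
- c = 0.9: 0.6454 / (0.6454 + 0.38) = 0.63 (simulated 0.62)

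Neither N nor eff appears in this expression, so a larger trial would not remove the bias. The loading c = 0.9 stands for a second depression scale such as PHQ-9.

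**3. How often it would be declared significant**

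There were 3,000 simulated trials per setting. Mediation was declared when both a and b were significant at two-sided 0.05. The lagged model used M at post to predict depression at the next wave, adjusted for arm, baseline M, and depression at baseline and post.

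| c | Same interval, eff 0.5 | Same interval, eff 0.8 | Lagged, eff 0.5 | Lagged, eff 0.8 |
|---|---|---|---|---|
| 0.5 | 8.4% | 18.4% | 0.6% | 1.3% |
| 0.6 | 15.0% | 31.5% | 0.5% | 1.8% |
| 0.7 | 23.2% | 46.4% | 1.5% | 2.3% |
| 0.8 | 28.8% | 64.5% | 1.6% | 3.3% |
| 0.9 | 41.7% | 80.7% | 2.3% | 3.3% |

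**4. Sensitivity to the assumptions**

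Other assumed variance structures and tests, at a loading of 0.6, gave same-interval rates of 7% and 19%, of 24% and 46%, and of 27% to 61%. For a near-duplicate depression scale, one gave 53% to 93%. Lagged rates, where computed, ran from under 1% to 5%.

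**5. What the lagged model loses**

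When mediation was made wholly real but completed within one wave, the same-interval model detected it in 58% to 91% of trials under one set of assumptions and in 61% to 98% under another. The lagged, adjusted model detected it in about 0.5% to 3% and in 3% to 5%. Part of its low false-positive rate is therefore low power for a fast mechanism.

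**The case against.** The strongest reply is that the article does not specify the model being criticised. A multilevel framework accommodates lagged, cross-lagged and same-interval models, and relating changes to changes is ordinary wording for a mechanism question. Lags and adjustment sets for an exploratory analysis are commonly left to an analysis plan. The design collects early ratings, and the introduction shows awareness that precedence matters. PHQ-9 has a stated purpose that is not mediation, and the Discussion's narrower wording suggests that it was never meant as a mediator. The simulated rates come from assumptions, and the adjusted lagged model can miss a true, fast mechanism.

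Most of this stands as a limit on the claim. A reader might infer that reverse causation will be reported as mechanism. The text does not support that, because no section commits to same-interval changes or rules out a lag. A reader might also infer that ZUF-8 and WAI would be run as mediators, but without a baseline they have no change to analyse. Nor does the introduction treat precedence as the only evidence of mechanism, since it also cites a mediation study.

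Two things survive. The mediator set is stated, not merely omitted, and read with the Secondary Outcomes section it includes a measure of the outcome construct. And the one sentence that describes the analysis pairs change with change, which leaves open the version that cannot answer the question.

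**Conclusion.** The point holds in a limited form. The stated mediator set includes PHQ-9, which makes that analysis circular, and the Exploratory Analyses section does not agree with the narrower descriptions in the introduction and Discussion. No time order is fixed. If changes over the same interval are used, reverse causation cannot be separated from mediation, and the mechanism aim could be answered wrongly.

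The direction is robust, because it follows from the expression for the spurious proportion mediated. The size is not: false-positive rates from about 7% to over 90% all rest on assumed arm effects, loadings and variance structures. The consequence is confined to an exploratory analysis. The primary BDI-II comparison and the conduct of the trial are unaffected.

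**What to change.** Revise the Exploratory Analyses wording before the data are analysed:

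- Name the candidate mediators. Exclude PHQ-9 and use it only as a measure of depression. State that ZUF-8 and WAI are outside the set because they have no change score.
- Take the mediator before the outcome: core-belief, emotion and memory-burden ratings from before the sessions or at post, or post scores of the other scales, predicting BDI-II at FU1 and FU2.
- Adjust for baseline mediator, baseline BDI-II and depression at the time of the mediator (PHQ-9 before sessions, BDI-II or PHQ-9 at post).
- Report any same-interval change-on-change result as association only, not as evidence of mechanism.

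No new data are needed. The lagged, adjusted estimate is less precise and has little power for a mechanism completed within one wave, so a null result should not be read as absence of mediation. A lag also does not remove confounding of mediator and later depression by other causes, and the report should say so.
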